### **11.3 Symptom burden and health-related quality of life (Secondary)**

Symptom burden will be evaluated using the NYHA functional classification at baseline and during follow-up. Symptomatic improvement or worsening will be defined as a change of at least one NYHA class compared with baseline.

Health-related quality of life will be assessed at baseline and annually using the SF-36 to evaluate the impact of MR and its treatment on daily activities and overall well-being. Longitudinal changes in HRQoL will be interpreted using a minimal clinically important difference of  $\geq 5$  points (improvement or deterioration).

#### **11.4 Treatment success (Secondary)**

Treatment success will be evaluated using responder-based analyses derived from annual follow-up assessments. For patients undergoing mitral valve intervention, treatment success will be defined as the first follow-up assessment at which MR severity is  $\leq 2$ , in combination with improvement in symptom burden ( $\geq 1$  NYHA class) and/or improvement in HRQoL (SF-36 increase  $\geq 5$  points) compared with baseline. For patients managed conservatively, treatment success will be defined as clinical stability, characterised by the absence of heart failure hospitalisation or mitral valve intervention during follow-up, together with non-worsening MR severity and stable or improved symptoms and/or HRQoL. LV and LA remodelling parameters will be analysed as longitudinal outcomes but will not be used as sole determinants of treatment success.

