## **1 Introduction and rationale**

Mitral regurgitation (MR) affects more than 10% of individuals aged 75 years and older and is associated with adverse cardiovascular outcomes, including heart failure, increased hospitalizations, and mortality (1-3). Despite its prevalence, MR is often undertreated, leading to progressive disease, adverse cardiac remodelling, and diminished quality of life (HRQoL) (1, 4, 5). While advancements in diagnostic and therapeutic technologies have improved outcomes, optimal management strategies, particularly in asymptomatic patients, remain unclear due to discrepancies in guidelines and a lack of robust data (6-8). However, timely intervention has been shown to improve outcomes significantly (6).

The multicentre prospective Significant Mitral Insufficiency Limburg Evaluation (SMILE) registry aims to evaluate long-term outcomes in patients with moderate-severe MR in routine clinical practice, and to determine clinical and echocardiographic predictors of MR progression and treatment success. Through a multidisciplinary approach, the registry aims to align the progression of mitral valve disease and care pathways with individual patient needs, optimize treatment strategies, and enhance long-term outcomes, including survival and HRQoL.

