## 13 Appendix

| Category                                                           | Variable                                  | Type        | Details                                                                    |
|--------------------------------------------------------------------|-------------------------------------------|-------------|----------------------------------------------------------------------------|
| Baseline Characteristics                                    | Date of visit                             | Date        | Date of the initial visit                                                  |
|                                                                    | Gender                                    | Categorical | Male, Female                                                               |
|                                                                    | Age at baseline                           | Numeric     | Age in years at the time of the initial visit                              |
|                                                                    | Height                                    | Numeric     | Height in centimetres                                                      |
|                                                                    | Weight                                    | Numeric     | Weight in kilograms                                                        |
|                                                                    | NYHA (Dyspnea class)                      | Categorical | Dyspnea class (I, II, III, IV)                                             |
|                                                                    | Heart rhythm                              | Categorical | Sinus rhythm, Atrial fibrillation, Atrial flutter, Pacemaker rhythm, Other |
|                                                                    | Heart rate                                | Numeric     | Heartbeats per minute                                                      |
| Baseline and Follow-up
Echocardiographic
Parameters | Date of echocardiography                  | Date        | Date of the echocardiography                                               |
|                                                                    | LVEF (%)                                  | Numeric     | Left ventricular ejection fraction                                         |

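### After intervention, a patient already in NYHA I can meet the treatment-success definition only through an SF-36 gain of at least 5 points, because section 11.4 has no rule for patients who start in the best class

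*Protocol*

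**What the plan says.** Protocol section 11.4 defines success in two ways.

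- **Intervention.** "For patients undergoing mitral valve intervention, treatment success will be defined as the first follow-up assessment at which MR severity is" 2 or lower, "in combination with improvement in symptom burden" of one NYHA class or more "and/or improvement in HRQoL (SF-36 increase" of 5 points or more), each against baseline.
- **Conservative.** The event element reads "characterised by the absence of heart failure hospitalisation or mitral valve intervention during follow-up". A status element is required in addition and reads "together with non-worsening MR severity and stable or improved symptoms and/or HRQoL".

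Section 11.3 sets the threshold for symptomatic change at one NYHA class and for HRQoL change at 5 SF-36 points. The appendix records NYHA as "Dyspnea class (I, II, III, IV"), so nothing lies below class I.

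Section 4.2 sets no symptom criterion for entry, and section 1 states that "optimal management strategies, particularly in asymptomatic patients, remain unclear". Identifying predictors of treatment success is a secondary objective (section 2.2). Section 7.1 assigns it to multivariable logistic regression, stratified by management strategy only where appropriate.

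**The concern.** One definition asks for improvement and the other for stability. That can be defended for patients who start with symptoms. It breaks down for patients who start without them, because the symptom element cannot be met from class I. These are the patients whose management the introduction singles out as unsettled.

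Two things are at stake. First, an asymptomatic patient whose valve is repaired and who stays well can be recorded as a treatment failure. Second, baseline NYHA becomes part of the outcome. Classes II to IV have two routes to success after intervention and class I has one, so worse baseline NYHA will tend to predict success whatever its clinical role.

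**Working it through.** The Protocol gives no figure for this endpoint, so there is none to reproduce. The check applies the two rules of section 11.4 to the same patient course.

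**Rules as coded**

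- Intervention success = MR at follow-up ≤ 2 AND (NYHA falls by ≥ 1 class OR SF-36 change ≥ +5).
- Conservative success = no heart failure hospitalisation AND no mitral intervention AND MR not worse AND (NYHA not worse OR SF-36 has not fallen by ≥ 5).

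Two readings are assumed: the and/or is inclusive, and stable means not worse by the section 11.3 thresholds.

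**Results.** The intervention patient has MR grade 1 after repair. The conservative patient has MR grade III throughout and no events.

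| NYHA course | SF-36 change | Intervention rule | Conservative rule |
|---|---|---|---|
| I to I | −6, 0 or +4 | failure | success |
| I to I | +5 or +10 | success | success |
| II to I | any of the five values | success | success |
| II to II | −6, 0 or +4 | failure | success |
| II to II | +5 or +10 | success | success |

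Unchanged class III or IV behaves like II to II.

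**Reading the table**

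1. The two rules classify a stable NYHA I patient in opposite ways whenever the SF-36 gain is below 5 points, and alike at 5 points or more.
2. The difference between the rules exists for every unchanged NYHA class. What is special to class I is that the symptom route is closed from the start: the best attainable NYHA change is I − I = 0, and 1 is required.
3. The dependence on baseline NYHA therefore arises within the intervention group alone. Stratifying by strategy does not remove it.

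**Reference visit.** Section 11.4 says only baseline. The appendix ties baseline age to the initial visit, and no pre-procedure assessment is defined. If baseline is the initial visit, take a patient enrolled in class I who worsens to III, is treated in year 3 and returns to I. The NYHA change is again 0, so the patient fails unless SF-36 exceeds its enrolment value by at least 5 points.

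**Comparison within the Protocol.** Section 11.2 gives a separate progression rule to patients who start in the worst remodelling category. Section 11.4 has no counterpart for patients who start in the best NYHA class.

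**The case against.** Several stronger readings are tempting, and the Protocol does not support them.

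- **A reader might infer that every asymptomatic patient with a good repair is a failure.** The SF-36 alternative stays open. If the definition is read as the first visit at which all elements are met, it can be met at any one of the annual visits.
- **A reader might infer that NYHA I patients have little room to gain on the SF-36.** The Protocol gives no SF-36 mean, spread or ceiling for them. NYHA is recorded as a dyspnoea class, while the SF-36 is meant to capture daily activities and well-being more broadly.
- **A reader might infer that the endpoint is loaded against intervention overall.** Conservative success also requires freedom from heart failure hospitalisation and from intervention during follow-up, and intervention success requires neither. No stated objective compares success rates between strategies. Nor are the two patients in the same state: the conservative one may still have grade III MR.
- **Baseline as the initial visit is an inference** from the appendix. The reference visit could be settled in a statistical analysis plan that is not at hand.

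All of this stands and limits the claim. It does not remove the defect. Section 11.4 itself fixes the definition, the symptom element cannot be met from class I, and the predictor analysis inherits that even if the strategies are never compared.

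**Conclusion.** The point holds in conditional form: after intervention, a patient who stays in NYHA I with MR grade 2 or lower fails unless SF-36 rises by at least 5 points, while the same NYHA and SF-36 course under event-free conservative care succeeds. The predictor model will partly report this ceiling as if it were a clinical association.

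This follows from the wording of section 11.4, the NYHA scale and the thresholds in section 11.3, with the and/or read as inclusive. The part about deterioration after enrolment rests additionally on baseline meaning the initial visit, and is less certain.

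No numerical magnitude is claimed. It would need the share of intervention patients in NYHA I and the distribution of their SF-36 change, and the Protocol gives neither. One secondary endpoint and its predictor analysis are affected. The co-primary endpoints are not. The definition should be changed before this endpoint is analysed.

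**What to change.** In section 11.4:

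1. Add a best-category rule, parallel to the extreme-category rule in section 11.2. For intervention patients in NYHA I at baseline, the symptom/HRQoL element is met by remaining in NYHA I and/or no SF-36 fall of 5 points or more. This is the conservative standard, "stable or improved symptoms and/or HRQoL", so both groups meet the same test on this element. The MR requirement stays.
2. Keep the improvement rule for NYHA II to IV.
3. Report success and fit the predictor models separately for baseline NYHA I and II to IV, and separately by management strategy. Do not pool the two success definitions. The separation is needed because item 1 alone would still leave the outcome dependent on baseline NYHA, in another direction.
4. State that for intervention patients the reference is the last available assessment before the procedure and that only post-procedure visits count. Record the procedure date.

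**Cost.** A few sentences. NYHA, MR grade and SF-36 are already collected. The appendix lists cardiac interventions as a categorical item with no procedure date beside it, so that date has to be added.

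**Downsides.** The definition has two branches, and separate models have fewer patients each. No pre-procedure visit is scheduled, so the last annual assessment may precede the procedure by up to about a year.

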## 7 Statistical analyses

### 7.1 Baseline, primary, secondary outcomes

Analysis will begin with descriptive statistics to summarise baseline characteristics. Categorical variables will be presented as counts and percentages and compared using the Chi-square test. Ordinal variables will be reported as frequencies and compared using ordinal or non-parametric tests. Continuous variables will be presented as means ( $\pm$  standard deviations) or medians (interquartile ranges), depending on the distribution, and compared using the independent t-test for normally distributed data or the Mann–Whitney U test for non-normally distributed data.

Time-to-event outcomes, including all-cause mortality and time-to-first heart failure hospitalisation, will be analysed using Kaplan–Meier estimates and compared using the log-rank test. Associations between baseline characteristics and clinical outcomes will be evaluated using multivariable Cox proportional hazards regression models, with results presented as hazard ratios (HRs) and 95% confidence intervals (CIs). A minimum of 10 events per variable will be considered to ensure statistical robustness.

Longitudinal changes in echocardiographic parameters and HRQoL will be analysed using mixed-effects models to account for repeated measurements within patients. MR severity will be demonstrated as an ordinal outcome, while continuous echocardiographic measures and HRQoL outcomes will be analysed using linear mixed-effects models. Treatment success will be evaluated using responder-based analyses based on annual follow-up assessments, and predictors of treatment success will be analysed using multivariable logistic regression models, with results presented as odds ratios (ORs) and 95% CIs. Analyses will be stratified by MR aetiology and, where appropriate, by management strategy (conservative, catheter-based, or surgical). Missing data will not be imputed; primary analyses will be conducted using all available data, with sensitivity analyses performed in complete-case cohorts. Statistical significance will be set as a two-sided  $p$ -value  $< 0.05$ .

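### The conservative treatment-success rule in section 11.4 can class as clinically stable a patient whom section 11.3 defines as worsened in NYHA class or SF-36

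*Protocol*

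**What the plan says.** Section 11.4 of the protocol gives two definitions of treatment success.

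- **Conservative management:** "treatment success will be defined as clinical stability, characterised by the absence of heart failure hospitalisation or mitral valve intervention during follow-up", and then "together with non-worsening MR severity and stable or improved symptoms and/or HRQoL".
- **Mitral valve intervention:** "treatment success will be defined as the first follow-up assessment at which MR severity is" grade 2 or lower, "in combination with improvement in symptom burden" by at least one NYHA class "and/or improvement in HRQoL (SF-36 increase" of at least 5 points).

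Section 11.3 sets the thresholds for change on both scales. For symptoms: "Symptomatic improvement or worsening will be defined as a change of at least one NYHA class compared with baseline". For quality of life: "Longitudinal changes in HRQoL will be interpreted using a minimal clinically important difference of" at least 5 points, applied to improvement and deterioration alike.

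Section 7.1 describes how the endpoint is used: "predictors of treatment success will be analysed using multivariable logistic regression models". It adds no condition on worsening, and it states that missing data will not be imputed. Identifying predictors of treatment success is a secondary objective in section 2.2.

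**The concern.** The connector in the conservative rule is satisfied by either component alone. Section 11.4 does not use the worsening thresholds of section 11.3 to exclude anyone. So the two sections can give opposite descriptions of one patient. Someone who moves from NYHA II to IV with an unchanged SF-36, with no heart failure admission, no intervention and no rise in MR grade, is symptomatically worsened under 11.3 and clinically stable under 11.4. The same holds for someone with unchanged NYHA class and a large SF-36 loss.

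What is at stake is the meaning of a binary outcome. If the group coded as successes contains patients who worsened by the protocol's own definition, the reported proportion does not describe stability. The odds ratios for its predictors then describe a mixture. The wording also allows two analysts to code the same patient differently, because one may read the connector as a plain 'and'.

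**Working it through.** The protocol states no success rate, sample size or power for this endpoint, so there is no figure to reproduce. The check is a truth table.

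**Inputs.** NYHA: improved, stable or worse, with a cut of one class (11.3). SF-36: improved, stable or worse, with a cut of 5 points (11.3). 'Stable' is taken to mean neither improved nor worse. All other conservative conditions (no heart failure admission, no mitral intervention, MR not worse) are taken as met.

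**Conservative rule as written:** pass if NYHA is not worse OR SF-36 is not worse.

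| | SF-36 improved | SF-36 stable | SF-36 worse |
|---|---|---|---|
| NYHA improved | pass | pass | pass, worse on SF-36 |
| NYHA stable | pass | pass | pass, worse on SF-36 |
| NYHA worse | pass, worse on NYHA | pass, worse on NYHA | fail |

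Passing cells: 9 − 1 = 8. Passing cells with a worsening defined in 11.3: 2 + 2 = 4. If neither scale may worsen, 2 × 2 = 4 cells pass.

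A patient in NYHA IV at baseline cannot move to a worse class. The symptom condition is then always met, and the SF-36 cannot change the classification.

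**Intervention rule as written:** pass if NYHA improved OR SF-36 improved. Passing cells: 3 + 3 − 1 = 5. Of these, 2 show opposite changes on the two scales; the other 3 contain no worsening.

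**Illustration of size (assumed inputs, this component only).** Suppose that among conservative patients NYHA improves, stays stable or worsens in 15/60/25%, and SF-36 in 25/40/35%. With independent changes:

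- either not worse: 1 − 0.25 × 0.35 = 0.9125
- neither worse: 0.75 × 0.65 = 0.4875
- share of those passing who worsened on one scale: (0.9125 − 0.4875) / 0.9125 = 0.466

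Simulating correlated changes (bivariate normal latent scores, 2,000,000 draws, same marginals) gave:

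| Latent correlation | Either not worse | Neither worse | Share of passes worse on one scale |
|---|---|---|---|
| 0 | 0.913 | 0.487 | 0.466 |
| 0.3 | 0.876 | 0.525 | 0.401 |
| 0.5 | 0.848 | 0.552 | 0.349 |
| 0.7 | 0.816 | 0.584 | 0.285 |

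None of these marginals or correlations comes from the protocol.

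**The case against.** **The wording may have been meant as 'and'.** Clinical stability is the governing term, and if both scales must be stable the problem disappears. This stands as a point about intent. The text does not settle it, however, and the ordinary sense of the connector is that either component suffices. The sentence needs repair on either reading.

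**The other conditions filter out deteriorating patients.** Freedom from heart failure admission, freedom from intervention and a non-worsening MR grade probably remove worsening patients more often than others. This stands against any use of the illustrative percentages as estimates. It does not remove the defect, because a decline in NYHA or SF-36 without an admission, an intervention or a rise in MR grade passes all three filters.

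**Many of the worsened patients would have changed little.** If SF-36 change had mean 0 and an SD of 10 to 15 (assumed), a fall of at least 5 points would occur in Φ(−5/10) = 31% to Φ(−5/15) = 37% of patients, many of them only just past the threshold. That is fair, and large losses should not be taken as typical. The threshold is nevertheless the protocol's own.

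**Deterioration is visible elsewhere.** SF-36 is analysed separately with mixed models, and NYHA worsening has its own definition. This limits the harm to overall reporting. It does not help the logistic model, whose outcome is the composite.

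**Stronger readings that a reader might infer.** One is that the intervention rule has the same error. It does not: MR grade 2 or lower plus improvement on at least one scale is a coherent responder rule, and it meets a defined worsening only in the two cells with opposite changes. Tightening it is a preference. Another is that the looser conservative rule biases a comparison of management strategies. Section 7.1 plans stratification by strategy where appropriate, but the protocol states no head-to-head comparison of success, and the two definitions differ by design. The NYHA IV case is a limit of the scale, and the protocol gives no frequency for it.

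**Conclusion.** The point holds for the conservative rule only. Read literally, section 11.4 accepts as clinically stable four NYHA by SF-36 combinations, out of eight that pass, which section 11.3 defines as a worsening on one scale. A patient worse on both scales fails, so the defect concerns worsening on one scale. The count rests on the literal reading of the connector and on the section 11.3 thresholds, and on no assumption about frequencies.

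The number of patients affected is unknown. The illustrative 29% to 47% depends wholly on assumed marginals and correlations, covers this one component, and ignores the admission, intervention and MR conditions. It must not be read as the share of conservative successes that are misclassified.

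The endpoint is secondary, in an observational registry. The correction is nonetheless worth making: section 11 fixes the definition, it conflicts with the section before it, and the repair is small.

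**What to change.** In section 11.4, for conservatively managed patients, replace the either/or wording with: neither NYHA class worsened by one or more classes nor SF-36 fell by 5 or more points from baseline (thresholds of section 11.3).

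Because section 7.1 rules out imputation and the SF-36 depends on a returned questionnaire, add a rule for incomplete data. Classify on the available measure when the other is missing, with a sensitivity analysis restricted to patients who have both. Report the present either/or rule as a further sensitivity analysis.

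The intervention rule may stay as it is. Counting patients with opposite changes on the two scales separately is optional.

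**Cost.** A short text change and no new data, since NYHA and annual SF-36 are already collected. The conservative success proportion will be lower. Patients without an SF-36 are classified on NYHA alone, which is a less demanding test than the two-scale rule; the sensitivity analysis in patients with both measures shows how much that matters. Sections 11.3 and 11.4 do not say which SF-36 score the 5 points apply to. The revised rule inherits that, so the score should be named there or in the analysis plan.
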